***Inoculation***

• Inoculation - using a P200 micropipette, 0.1ml saline containing the desired dose (see
Figure 2) of pneumococcus will be instilled into the nose. The participant will be seated in a semi-recumbent position. After inoculation, the participant will remain in this position for up to 15 mins. They will be given a post-inoculation advice sheet (including emergency contact details), thermometer, a course of amoxicillin (500mg TDS for 3 days) and a daily symptom log to complete.

• Dose escalation and sham inoculation - We have adopted a step-wise approach to escalating the inoculation dose. The protocol is designed to: a) minimise the possibility that we try repeatedly to attain carriage at a dose in which it is unlikely to occur; b) maximise safety by inoculating small groups (in case adverse events occur) before continuing on to larger groups in which we will be able to give reasonable precision to estimate carriage rates. Groups 1, 2 and 3 will receive increasing doses of pneumococcal inoculation as explained in
Figure 2. Briefly, 20,000 cfu/naris (Group 1) is not expected to achieve carriage. If 80,000 cfu/naris achieves more than 4 from 9 participants with carriage, then the study will end at that point. Sham inoculation with 0.9% normal saline has been incorporated into the study design to assess whether any potential observed effects in participants are pneumococcal challenge-related or simply reflect the study conditions. Participants will receive only one inoculation dose. If carriage is not achieved after inoculation, participation will be concluded upon completion of visit eight.

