**Figure 2. f2:**
[figure not shown]
Dose escalation study design, adapted from Waddington
*et al*.
^12^. The doses for Groups 1, 2 and 3 will be 20000, 80000 and 160000 pneumococcal colony forming units (CFU) per naris respectively. All participants will be monitored for adverse effects and for pneumococcal carriage. The first cohort will be inoculated with 20,000 CFU/naris (
**Inoculation A**).
**†**: Eight participants will be randomised 3:1 to pneumococcal inoculation (n=6) or sham inoculation with 0.9% saline (n=2). If ≥2/6 participants from the initial cohort of eight develop experimental pneumococcal carriage, a further 4 participants will be recruited to this dose cohort.
*****: Four participants will be randomised 3:1 to pneumococcal inoculation (n=3) or sham inoculation with 0.9% saline (n=1). If the combined carriage rate of the completed cohorts is ≥4/9 (6+3 nasally challenged with pneumococcus), then the nasal challenge dose will be established, and we will conclude the study. If at either of these decision points, the carriage rate is insufficient, the algorithm will be restarted with a higher challenge dose of 80,000 CFU/naris (
**Inoculation B**) and the recruitment schedule repeated. If at 80,000 CFU, the carriage rate is insufficient, then an additional cohort of participants will be recruited to the 160,000CFU/naris dose escalation group (
**Inoculation C**).
**‡**: 12 participants will be randomised 3:1 to pneumococcal inoculation (n=9) or sham inoculation with 0.9% saline (n=3). We have previously demonstrated 50-60% carriage rates with the 80,000 CFU 6B dose in the Liverpool pneumococcal controlled human infection model
^6,
13^.

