Figure 2 since an alternative participant will be recruited in the case of withdrawal of a participant. Participants missing study visits so that no day 2, 7 or 14 data is available will be withdrawn from the study and their data excluded from data analysis. A new participant will be recruited in such a case and this new participant will be allocated to the same pneumococcus / sham inoculation as the participant ID for the withdrawn participant was randomised to. The primary feasibility endpoint will be assessed, at each of the five analysis time points using colonisation results data from all participants that are required for that stage’s analysis and that have completed visit 7 (d14). Other analyses are primarily descriptive or make use of censored data techniques, so that no advanced missing data methods will be used in these analyses. Data collection forms are provided in extended data
^21^. 

***Statistical significance and multiple testing.*** Success (feasibility) of the study will be decided according to the decision rules stated on
Figure 2.

Success (safety) of the study will decided by decision of the DSMB & TC upon revision of each SAE and SUSAR. For this reason, no formal null hypothesis significance testing will be performed for the main analysis and no multiple testing adjustment will need to be made.

For secondary analyses, statistical significance is defined as p<0.05, but effect sizes / parameter estimates, exact p-values and confidence intervals will be stated. While we will report on statistical significance, results will be presented and discussed in accordance with recent guidance
^22^.

***Technical details.*** All analyses and figures will be performed using the R environment (v.3.5.3 or later) for statistical computing and graphics and associated packages
^23^.

***Feasibility.*** The primary analysis aims to establish feasibility of the Malawi CHIM: does one of the three doses (20,00, 80,000, 160,000 CFU) lead to ≥50% nasal colonisation?

To assess this, the decision algorithm specified in the study design (

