Figure 2) is followed and no statistical analysis is required. However, we will complement this with a number of descriptive and secondary analyses: For each inoculation dose used in the study, we will estimate colonisation (by serotype 6B) rates and compute 95% exact, binomial confidence intervals. We will also compute this for participants inoculated with the sham, saline solution. If more than 1 dose is used in the study, we will plot the estimated colonisation rate against inoculation dose for a crude estimate of the dose-response curve. For each inoculation dose, we will also plot time curves of colonisation rates at visits 0 (d-5), 4 (d2), 6 (d7), 7 (d14). We will also use lytA qPCR to assess nasal carriage by
*Streptococcus penumoniae*. We will repeat all analyses using this method of carriage detection. Further, for the qPCR results, we will estimate average carriage densities and associated 95% confidence intervals for each challenge dose. If more than one dose is used, we will also plot individual carriage densities against inoculation dose for a crude estimate of the carriage density dose response curve. We will estimate the lower limits of detection and quantification for the qPCR data, then use censored data techniques to account for the uncertainty associated with values below these limits.

We will compile a summary table for demographic (age, sex), baseline physiological (pulse rate, oxygen saturation on room air, systolic blood pressure, diastolic blood pressure, tympanic body temperature, height, weights, BMI, baseline carriage of
*S. pneumoniae* other than serotype 6B) and baseline immunological variables. Baseline physiological and immunological variables are those measured at the inoculation visit or for which the sample was taken at the inoculation visit (prior to the inoculation). Analogous tables will be compiled for the assessments made at visits 2–8.

***Safety.*** AEs, SAEs, SUSARs are monitored throughout the study and any decision to stop the trial is taken by the TSC in consultation with the DSMB. At study end, AEs, SAEs and SUSARs will be listed by type and by inoculation group (sham,

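### The primary question asks for at least 50% colonisation, but the deciding rule passes at 4 of 9 (44%); a pass does not show 50%, and nine people do not give the claimed precision

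*Protocol article*

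**What the plan says.** All references are to the Protocol article.

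- **Primary question** (Statistical analysis, Feasibility): does one of the three doses "lead to ≥50% nasal colonisation"?
- **How it is answered** (same paragraph): the Figure 2 algorithm "is followed and no statistical analysis is required". The paragraph on statistical significance confirms this: "Success (feasibility) of the study will be decided according to the decision rules stated on" Figure 2. The Feasibility paragraph then adds descriptive analyses, including an exact binomial 95% CI for each dose.
- **First step** (Figure 2 legend): "If ≥2/6 participants from the initial cohort of eight develop experimental pneumococcal carriage", four more participants join that dose cohort, three of them challenged.
- **Final step** (Figure 2 legend): the condition for a pass reads "If the combined carriage rate of the completed cohorts is ≥4/9 (6+3 nasally challenged with pneumococcus"). Meeting it settles the dose and ends recruitment.
- **Competing threshold** (Inoculation, dose escalation): "If 80,000 cfu/naris achieves more than 4 from 9 participants with carriage", the study ends there.
- **Precision** (same bullet): the design moves to "larger groups in which we will be able to give reasonable precision to estimate carriage rates".
- **Target elsewhere** (Study aims, Study hypothesis): approximately 50% carriage, not a minimum of 50%.
- **Sample size justification**: a feasibility study with no formal power calculation, meant to find out whether experimental carriage is possible in Malawi.

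**The concern.** The article states a question, a rule and the link between them, and the three do not fit. A dose seen to colonise 4 of 9 people, an observed 44.4%, would count as a yes to a question about at least 50%. The threshold is also worded in two ways: exactly 4 carriers of 9 at 80,000 CFU per naris would end the study under Figure 2 but not under the Inoculation section.

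Even when the observed rate is above 50%, nine people say little about whether the true rate is. The precision claim suggests otherwise. In addition, the rate observed at a selected dose has been filtered by the rule, because a dose passes only if its count is high enough. The rate is then reported as if it were unselected. At stake is what the trial may conclude: that a dose was selected because enough carriage was seen, or that it gives at least 50% carriage.

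**Working it through.** **Inputs.** From the Figure 2 legend: 6 challenged, continue if at least 2 carry; then 3 more challenged, pass if at least 4 of 9 carry. From the Inoculation section: more than 4 of 9, i.e. at least 5. The 160,000 cohort has 9 challenged and 3 sham in one step. Interval method: exact binomial 95%, as planned.

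**The plan's own figures.** Maximum sample size is 3 doses × (8 + 4) = 36. Maximum number of assessments is 2 + 2 + 1 = 5. Both agree with the article, so this reading of the design is the intended one.

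**Threshold against question.** 4/9 = 44.4%, below 50%. 5/9 = 55.6%, above 50%.

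**Pass probability for one dose.** Let X1 ~ Bin(6, p), X2 ~ Bin(3, p), and r the final threshold.

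P(pass) = Σ over x = 2,…,6 of P(X1 = x) × P(X2 ≥ r − x)

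For p = 0.40 and r = 4:

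- x = 2: 0.3110 × 0.352 = 0.1095
- x = 3: 0.2765 × 0.784 = 0.2168
- x = 4, 5 or 6 (already at 4): 0.1382 + 0.0369 + 0.0041 = 0.1792
- Sum: 0.505

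| True rate | P(pass), at least 4/9 | P(pass), at least 5/9 |
|---|---|---|
| 20% | 8.2% | 2.0% |
| 30% | 26.2% | 9.9% |
| 40% | 50.5% | 26.7% |
| 50% | 73.4% | 50.0% |
| 60% | 89.3% | 73.3% |

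Both columns use the same first step of at least 2 of 6.

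**Precision.** Exact (Clopper–Pearson) 95% limits for x carriers of 9 are the 2.5% quantile of Beta(x, 10 − x) and the 97.5% quantile of Beta(x + 1, 9 − x).

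- 4/9: 13.7% to 78.8%, width 65.1 points
- 5/9: 21.2% to 86.3%, width 65.1 points
- 7/9: 40.0% to 97.2%
- 8/9: 51.8% to 99.7%, the first count whose lower limit exceeds 50%

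**Observed rate given a pass (at least 4/9).**

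E(observed rate | pass) = Σ over passing (x, y) of [(x + y)/9] × P(X1 = x) P(X2 = y), divided by P(pass)

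| True rate | Mean observed rate among passes | Excess (points) |
|---|---|---|
| 20% | 47.5% | 27.5 |
| 30% | 49.9% | 19.9 |
| 40% | 53.1% | 13.1 |
| 50% | 57.5% | 7.5 |
| 60% | 63.5% | 3.5 |

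The excess is largest where the true rate is furthest below the threshold.

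**The case against.** The strongest reply is that this is a feasibility study with no power calculation and no formal test in its main analysis. Its aim is about 50%, and 4 of 9 is as close to half as nine people can come from below. That stands for the sample size and for the aim. It does not cover the Feasibility paragraph, which turns the aim into a minimum of 50% and gives that question to a rule that passes below it.

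Second, the remark that no statistical analysis is required might be read as meaning that nothing else will be reported. The documents do not support that reading: exact CIs per dose are planned, so a pass at 4/9 would appear with 14–79% beside it. But those intervals do not enter the decision and do not allow for selection.

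Third, the stricter wording in the Inoculation section would put the observed rate above 50%. True, but the statistical section names Figure 2 as governing, and the interval at 5/9 is just as wide.

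Four stronger readings are tempting and go too far:

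- **No pass could ever support 50%.** The exact lower limit does exceed 50% at 8/9 and 9/9. Nor is 8/9 a fair standard for this rule: a dose with a true rate of exactly 50% has 8 or 9 carriers of 9 only 2% of the time (10/512).
- **The three-dose sequence nearly always succeeds.** Assumed true rates of 20/30/40% give 67% and 30/40/45% give 87%, but only if at least 4 of 9 also applies at 160,000, where the text shown gives no threshold. The first two doses alone give 32% and 64%. The dose-response rates are also assumptions, and the article does not expect carriage at 20,000.
- **A passing dose shows about 50% whatever its true rate.** The mean runs from 47.5% to 63.5% over true rates of 20% to 60%. The bias is upward, not to a constant.
- **The later vaccine study will be sized on this rate.** The article says only that the later study will be based on a completed UK trial.

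**Conclusion.** The point holds as an inconsistency between question, rule and precision claim. The governing rule can answer yes at an observed 44.4%. A dose with a true rate of 40% passes about half the time (50.5%), or 26.7% of the time if 5 of 9 is required, so under neither wording does a pass show at least 50%. At most nine challenged per dose gives an interval about 65 points wide at either threshold, which is not reasonable precision. Under the 4-of-9 rule, the observed rate at a passing dose averages 49.9% when the truth is 30% and 53.1% when it is 40%.

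These per-dose figures assume only independent participants with a common true rate and the two-stage rule as written for 20,000 and repeated at 80,000. They need no assumption about 160,000. The defect lies in what may be concluded, not in running a small dose-finding study. A table of pass probabilities may be in the analysis plan, which is not shown, so its absence here is not part of the point.

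**What to change.** 1. Reconcile the three statements: at least 50% in the Feasibility paragraph, at least 4 of 9 in Figure 2, and more than 4 of 9 in the Inoculation section. Which threshold is intended is for the investigators to say; it should then read the same everywhere, and the count that applies at 160,000 should be stated too.
2. Restate the primary question as what the rule decides: a dose is selected because carriage reached the stated count among nine challenged participants, a result compatible with the aim of about 50%. Do not conclude at least 50% from a pass.
3. Replace the claim of reasonable precision with the actual exact interval, for example 14–79% at 4/9 and 21–86% at 5/9.
4. Beside the planned CIs, state that the rate at the selected dose is conditional on passing and tends to be too high, with the size given under the chosen rule.
5. If overall pass rates across the three doses are quoted, label the 160,000 threshold and the dose-response rates as assumptions.

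The cost is wording and a short calculation. No participants, visits or procedures are added. The price is a weaker stated conclusion.

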### Safety considerations and assessment

***Study design to ensure safety.*** Safety is paramount in human infection studies. While the risk to individuals of developing any infection is very low (40% Malawian adults experience natural colonisation at any time, and the incidence of invasive disease is 20/100 000 patient years
^5^), the study is designed to ensure any risk is minimal by appropriate:

Study team selection and rigorous training in human challenge proceduresStudy design with staggered recruitment approach (sample size and dose)Careful serotype selection and dosing based on 10 years of LSTM experienceParticipant selection and exclusion criteria as detailedParticipant education through a participant information sheet (provided)Rigorous safety procedures including daily monitoring and providing participants with a thermometer and a course of amoxicillin tablets in case of emergency
^14^
24-hour emergency telephone contact with researchers, including close individual daily monitoring, and access to hospital facilities and prompt treatment if requiredTo further mitigate risk, participants will be provided with accommodation at the Grace Bandawe Centre for three nights immediately following nasal challenge. If a participant determines that it is not possible to stay at the Grace Bandawe Centre for three nights then a pragmatic approach to further study procedures will be taken. If the participant can demonstrate that they remain readily available by phone and accessible with transport, this need not affect the procedure. Twice daily checks could replace the resident period. In the Liverpool CHIM there is no resident period at all. If, however, the participant absconds or is intending to be uncontactable, then participation in the study will be stopped and antibiotics offered as at the end of the protocol.

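### The lytA qPCR repeat of the serotype 6B analyses measures any pneumococcal carriage, so its rates, dose-response plots and densities by dose do not describe experimental colonisation

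*Protocol article*

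**What the plan says.** All of the planned wording is in the protocol article, mostly under Statistical analysis, Feasibility.

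- **Culture.** For each dose, "we will estimate colonisation (by serotype 6B) rates and compute 95% exact, binomial confidence intervals". The same is done for sham participants. Rates are plotted against dose if more than one dose is used, and over time from d-5 to d14.
- **qPCR rates.** "We will also use lytA qPCR to assess nasal carriage by" the species *S. pneumoniae*, with no serotype qualifier. Then: "We will repeat all analyses using this method of carriage detection".
- **qPCR density.** "for the qPCR results, we will estimate average carriage densities and associated 95% confidence intervals for each challenge dose", and with more than one dose "we will also plot individual carriage densities against inoculation dose for a crude estimate of the carriage density dose response curve". Limits of detection and quantification will be estimated, "then use censored data techniques to account for the uncertainty associated with values below these limits". No restriction to carriers, or to 6B carriers, is stated.
- **Who is in the analysis.** Under Screening and preliminary assessment, a participant with natural carriage continues and is inoculated, unless the natural serotype is 6B. Baseline carriage of other serotypes is one of the tabulated baseline variables.
- **How common natural carriage is.** Safety considerations and assessment states that "40% Malawian adults experience natural colonisation at any time".
- **What decides the study.** The primary endpoint is culture of the inoculated pneumococci (Study endpoints), and success follows the Figure 2 rules.

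**The concern.** Between the two sets of analyses the quantity measured changes from the inoculated serotype to the whole species, while the display by challenge dose stays the same. Natural carriers of other serotypes are in the denominator by design, so a positive lytA result after challenge may have nothing to do with the inoculum. The 20,000 CFU group, in which the article expects no carriage, could show substantial positivity by qPCR.

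Density has the same problem and one more. Non-6B organisms add to the measured density. In addition, censoring is planned at the detection limit and the population is not stated. If every participant entered the average, uncolonised people would be treated as carriers at an unseen low density, and the mean would reflect how many were colonised as well as how densely.

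At stake is the molecular read-out of a study that aims to confirm assays relevant to vaccine testing and to prepare for later challenge studies. Read as experimental colonisation, it would overstate the rate at every dose and flatten the dose-response.

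**Working it through.** **No stated figure to reproduce.** The article gives no expected qPCR rate and no power. The Figure 2 design does reproduce the maximum sample size: (8 + 4) + (8 + 4) + 12 = 36, of whom 27 are challenged and 9 receive sham, so at most 9 are challenged per dose.

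**Inputs for the rates**
- Natural carriage *n*: 40% (Safety considerations and assessment). This describes Malawian adults in general. The trial excludes people with HIV infection, smokers, recent antibiotic users and those in close contact with children under 5, so enrolled participants may carry less. Positivity at any of several visits may, on the other hand, exceed a point prevalence. I therefore show 10 to 40%; only the 40% comes from the document.
- 6B rate *e*: about 0 at 20,000 CFU (Inoculation) and about 50% at 80,000 CFU (Study hypothesis).
- Assumption: natural non-6B carriage and 6B acquisition are independent.

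**Formula.** P(lytA positive) = 1 − (1 − e)(1 − n). The contrast between e = 0 and e = 0.5 is 0.5 × (1 − n).

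| Natural carriage | qPCR rate, 6B rate 0% | qPCR rate, 6B rate 50% | Contrast (true: 50 points) |
|---|---|---|---|
| 10% | 10% | 55% | 45 |
| 20% | 20% | 60% | 40 |
| 30% | 30% | 65% | 35 |
| 40% | 40% | 70% | 30 |

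At 40% natural carriage, true 6B rates of 0, 10, 30 and 50% read as 40, 46, 58 and 70%. Of the positives in a 50% dose group, (0.70 − 0.50)/0.70 = 29% would carry no 6B. Of 9 challenged participants at a dose, 9 × 0.4 = 3.6 would be natural carriers.

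**Can the sham group correct this?** Not within a dose. There are 2 or 3 sham participants per dose, and the exact 95% interval for 1/3 runs from 0.8% to 90.6%.

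**Density, conditional on how it is done.** Suppose all participants entered one left-censored normal model on the log10 scale. Assumed inputs, none from the document: carriers with log10 mean 3 and SD 1, and a detection limit of log10 1. The large-sample fit gives:
- 50% positive (no natural carriage): mean 1.13, which is 3 − 1.13 = about 1.9 log10 below the carriers' mean.
- 70% positive (50% 6B rate with 40% natural carriage): mean 2.08, which is 3 − 2.08 = about 0.9 log10 below.

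The fitted mean moves by 2.08 − 1.13 = 0.95 log10 between these two cases although density among carriers is the same in both.

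**The case against.** The strongest reply is that the article does not mislabel anything. It uses colonisation by 6B for culture and carriage of the species for qPCR, and as an estimate of any pneumococcal carriage a rate of 40% or 70% is correct. Repeating every analysis also gives qPCR rates for sham and at d-5, and baseline non-6B carriage is tabulated, so a careful reader has context. This stands in part: the article never calls the lytA rate 6B colonisation. But it repeats the 6B dose-response display with a different quantity and no serotype restriction, and neither the sham nor the d-5 values separate 6B from other serotypes after challenge.

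A reader might infer that dose selection is at risk. The documents do not support that: the primary endpoint and the escalation rule use culture of the inoculated strain, and the qPCR work is described as complementary and its curves as crude. A reader might also infer that natural carriage creates a false dose trend. In expectation it does not, because it raises all groups alike and flattens the trend; only chance imbalance among 6 to 9 challenged participants per dose could distort it.

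On density, the article does not say that one censored model will be fitted to everybody. Average carriage density could mean density among carriers, and the full analysis plan, not shown here, may settle this. That also stands. The density bias is therefore conditional, although the stated censoring at the detection limit leaves it open.

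**Conclusion.** The point holds for the secondary, descriptive qPCR analyses only. As written, the lytA rates, dose-response plots and densities by dose measure any pneumococcal carriage and cannot be read as experimental colonisation. With natural carriage of 10 to 40%, a dose with no 6B reads 10 to 40%, and a true 50-point contrast reads as 45 down to 30 points. The change of target from 6B to species rests on the article's own wording. The size rests on independence and on where enrolled participants fall in that range.

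The further claim, that the mean density mixes colonisation rate with density, holds only if all participants enter as left-censored. Its size (about 0.9 to 1.9 log10 below the carriers' mean with 70% down to 50% positive) depends wholly on assumed inputs and should not be quoted as a property of this trial. The change is worth making because it is cheap and the read-out informs later studies.

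**What to change.** 1. State that lytA rates, time curves and dose plots are of any pneumococcal carriage, and show them beside the d-5 and sham values that the repeat already produces.
2. For experimental colonisation by qPCR, add an analysis restricted to participants lytA-negative at d-5.
3. Estimate log10 density by dose among 6B culture-positive participants, and flag those with baseline non-6B carriage, whose lytA density may include both strains.
4. Apply censoring only to detected values below the quantification limit.

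**Cost.** Items 1, 3 and 4 are analysis wording and use culture and qPCR results already planned. Item 2 uses the d-5 washes already scheduled, but at 40% natural carriage it keeps about 60% of participants (9 × 0.6 = 5.4 of 9 challenged at a dose, or 6 × 0.6 = 3.6 of 6), and it does not remove natural acquisition after d-5. A 6B-specific PCR target would answer the question more directly, but it is an additional assay and not a change of wording, so it is optional.

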### Screening and preliminary assessment

Following consent, inclusion and exclusion criteria, data and samples will be collected.

• Clinical examination - the initial clinic visit will include a focused clinical history and targeted clinical examination involving auscultation of the lung fields and heart sounds. Participants will be informed if their clinical examination is normal. Should a previously unrecognised abnormality be identified, this will be explained to the individual, and appropriate investigations and follow-up will then be arranged by the study team. Further participation will be determined at the discretion of the study doctor dependent on the nature of the abnormality detected. If the participant is not eligible due to an acute illness, they may be re-screened at a later date with their verbal consent.

•
*Nasal wash* - will be performed using our published method
^11^. This is a well-used and validated technique to collect nasal bacterial specimens used successfully by the Liverpool CHIM team who will rigorously train the Malawi team. Briefly, 5ml of sterile saline is instilled and held for a few seconds in the nares before being expelled into a sterile Galli pot. This is repeated twice in each naris using 20ml saline in total. In the event of nasal wash loss (defined as cough/sneeze/swallow), the procedure may then be repeated to obtain an adequate specimen. Should the nasal wash reveal natural colonisation of pneumococcus, the participant will continue in the study and receive the inoculation as per protocol, unless the natural serotype is identified as 6B, in which case the patient then leaves the study at day 2. All pneumococcal carriage negative participants will continue in the study.

•
*Nasosorption strips* - Nasosorption will be obtained before a nasal wash and/or inoculation. The strips are like blotting paper developed by Hunts Development Ltd (UK, catalogue number: NSFL-FXI-11). They collect concentrated nasal lining fluid before the nasal wash to measure inflammatory responses induced by infection that may be associated with increased colonisation density and acquisition. Concentrate nasal fluid will be used to measure cytokine levels by multiplex bead array. Blotting paper will be held inside the nostril for up to 3 minutes until soaked, removed and placed in the microcentrifuge tube for storage.

•

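### The lytA qPCR repeat of the serotype 6B analyses, and the only density analyses, measure any pneumococcus and not the challenge strain, because natural non-6B carriers are inoculated and kept

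*Protocol article*

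**What the plan says.** All places are in the protocol article.

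- *Statistical analysis*, Feasibility: for each dose, "we will estimate colonisation (by serotype 6B) rates and compute 95% exact, binomial confidence intervals". The same is done for sham participants, with a plot of rate against dose if more than one dose is used, and time curves at d-5, d2, d7 and d14.
- The same paragraph then adds a second assay: "We will also use lytA qPCR to assess nasal carriage by" *Streptococcus pneumoniae*, that is, the species. The next sentence is "We will repeat all analyses using this method of carriage detection".
- Density appears only for this assay: "for the qPCR results, we will estimate average carriage densities and associated 95% confidence intervals for each challenge dose", and, with more than one dose, "we will also plot individual carriage densities against inoculation dose for a crude estimate of the carriage density dose response curve".
- *Screening and preliminary assessment*, nasal wash: "Should the nasal wash reveal natural colonisation of pneumococcus, the participant will continue in the study and receive the inoculation as per protocol". The one exception is a natural strain identified as 6B; that participant leaves the study.
- *Safety considerations and assessment*: "40% Malawian adults experience natural colonisation at any time".
- *Determination of colonisation* mentions PCR only as a general method of detecting bacteria and names no serotype-specific target.

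**The concern.** The target moves from the challenge serotype to the species between two neighbouring sentences, with no restriction, stratification or change of label for the repeated analyses. A participant who arrives with a non-6B strain and keeps it will be lytA positive after challenge whether or not 6B was acquired. The density recorded will be that of the natural strain alone, or of both strains together. The lytA signal has no isolate that could be typed, so the serogrouping done on cultured colonies does not repair it.

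At stake is how the second detection method and the only density result are read. Natural carriage would tend to raise the lytA rate at each dose, including the dose at which no carriage is expected, and to compress the dose plot. The doses are given in sequence to cohorts of at most 9 challenged participants. A chance difference in the number of natural carriers between cohorts could therefore create or hide an apparent trend in rate or density.

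**Working it through.** The plan gives no figure for the qPCR rate, so there is none to reproduce. The check is how far a species-level rate departs from a 6B rate.

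**Inputs**
- Natural carriage n: 40% (*Safety considerations and assessment*, Malawian adults in general). The article gives no figure for the trial's own eligible group, so 20% and 10% are added as assumptions.
- True 6B carriage c: 0% (*Inoculation*: the 20,000 CFU dose is not expected to achieve carriage); 50% (*Sample size justification*: the 80,000 CFU dose in Liverpool); 25% as an assumed middle value.
- Challenged participants per dose: 6 + 3 = 9. Sham per dose: 2, or 3 if the dose cohort is completed (Figure 2 legend).

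**Assumptions.** Natural carriage is independent of 6B acquisition, persists through follow-up, and is always detected by lytA.

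**Formula.** lytA-positive rate = 1 − (1 − n)(1 − c). For example, with n = 0.40 and c = 0.25: 1 − 0.60 × 0.75 = 0.55.

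| Natural carriage n | c = 0% | c = 25% | c = 50% |
|---|---|---|---|
| 40% | 40% | 55% | 70% |
| 20% | 20% | 40% | 60% |
| 10% | 10% | 32.5% | 55% |

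**Dose contrast.** The expected difference between 20,000 and 80,000 CFU is 50 points for 6B. On lytA it is (1 − n) × 50 points: 30 at n = 40%, 40 at 20%, 45 at 10%.

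**Make-up of the positives.** At n = 40% and c = 50%, the share of lytA positives carrying only a natural strain is 0.40 × 0.50 / 0.70 = 0.29.

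**Carriers per dose.** At n = 40%, 9 × 0.40 = 3.6 of 9 challenged participants are expected to be natural carriers, and the chance of at least one is 1 − 0.60^9 = 0.99. The expected number without natural carriage is 9 × 0.60 = 5.4.

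**Density.** The documents give no densities for natural or experimental carriage, so neither the size nor the direction of the effect on mean density can be worked out from them.

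**The case against.** The strongest reply is that nothing decisive rests on qPCR. *Study endpoints* defines the primary endpoint by culture of the inoculated pneumococci. Feasibility follows the Figure 2 decision rules, and the qPCR work belongs to the complementary descriptive and secondary analyses. This stands. A reader might infer that natural carriers could trigger a wrong escalation or feasibility decision through lytA. The text does not support that: the decision algorithm is set apart from the list of analyses to be repeated, and nothing says the Figure 2 rule is re-applied to qPCR.

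Second, the plan already produces some background. Repeating all analyses yields a lytA rate in sham participants and a pre-challenge point at d-5, and baseline non-6B carriage is tabulated. This stands in part. With 2 to 3 sham participants per dose the background is imprecise, it does not separate strains within a person, and density is stated only per challenge dose, with no sham density.

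Third, the plan openly writes serotype 6B for one method and the species for the other. True, but the repeated analyses, including the density dose-response plot, are set against challenge dose without that distinction being carried through.

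Fourth, 40% refers to Malawian adults in general, whereas the trial excludes people with HIV infection, smokers, those in close contact with under-fives and those with recent antibiotic use. This also stands, and it is why the lower assumed values are shown.

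Finally, the separate SAP is not shown and may restrict the analysis or name a 6B target. The point is not that detail is missing: the article itself states an unrestricted repeat. If the SAP differs, the two should be reconciled.

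**Conclusion.** The point holds as a matter of labelling and stratification in descriptive, secondary analyses. As written, the lytA rates, time curves, densities and dose plots estimate carriage and density of any pneumococcus, not of the challenge strain. On the stated assumptions the excess over true 6B carriage is n(1 − c). When true carriage is 50%, that is 20 points at 40% natural carriage and 5 points at 10%; when no 6B carriage occurs, it is the whole of n. Clearance of natural strains, imperfect detection, or dependence between natural carriage and 6B acquisition would change these figures. Dose escalation and the feasibility conclusion are not affected.

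**What to change.** In *Statistical analysis*, Feasibility, replace the sentence that repeats all analyses with wording to this effect:

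1. All-comer lytA rates and densities are labelled *any pneumococcus* and shown beside the sham group, including sham density.
2. lytA rates, time curves, densities and dose plots are presented by carriage status before inoculation (culture and lytA at d-5). Only the baseline-negative group is read as an approximation to experimental carriage.
3. Non-6B isolates found after challenge are reported alongside, and the participants concerned are not excluded. Excluding them would condition on a post-challenge result and change the denominator from visit to visit.

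This needs wording in the protocol and SAP only and uses results already planned. The downside is smaller groups: about 5 of 9 challenged participants per dose would be baseline-negative at 40% natural carriage, so confidence intervals for these descriptive results will be wider.
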